#### Within-Trial Cost-Effectiveness

The cost-effectiveness analyses will take both a national health care perspective and, separately for the purpose of sensitivity analysis, a limited restricted societal perspective, including health care costs, patient costs (travel cost), and productivity costs for patients or their caregiver (in case the patient is a child aged <15 y). Cost-effectiveness will be reported in terms of the incremental cost-effectiveness ratio (ICER) expressed as the difference in costs divided by the difference in outcome, between patients in the intervention and control groups. Costs will be estimated from the time of initial contact (day 0) and over a follow-up period of 28 days and calculated by category. Due to the short duration of the study, costs and outcomes will not be discounted. Costs will be expressed in Euros, in 2024 conversion rates. Effect will be measured as the total number of recontacts within 7 days and quality-adjusted life years within 28 days. Quality-adjusted life years are calculated as the area under the utility curve for each patient based on patients’ health-related quality of life measured by EQ-5D-5L for patients aged >15 years (in Denmark, individuals become responsible for managing their own health care at the age of 15, therefore not a requiring parental intermediary or proxy completion of the EuroQoL 5-Dimension) and valued using Danish value sets [22,23]. Missing costs or quality-of-life data will be handled by multiple imputations. Differences in mean costs and effect will be estimated using separate generalized linear regression models, with appropriate distribution and link functions for costs and outcomes. The models will control for treatment, time point, treatment-by-period interaction as fixed effects, and cluster at the GP level as a random effect. Furthermore, the models will adjust for baseline health care cost (6 months before the initial contact) and baseline utility [24]. Nonparametric confidence intervals for costs, effect, and ICER will be computed using a 2-stage bootstrapping technique with 1000 replications [25] and the 2.5th and the 97.5th percentile of the 1000 bootstrap replications. Conventional methods for estimating uncertainty around the ICER, such as cost-effectiveness acceptability curves, will be applied as well. Sensitivity analyses will be conducted to test assumptions, uncertainty around variable estimates, and the robustness of results.

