### Allocation

The study is designed as a cluster randomized crossover study with the GP clinic as the unit of randomization, that is, all GPs affiliated to a GP clinic are randomized to either intervention (A) in the first period and usual care (B) in the second (AB sequence) or in the BA sequence. Allocation of the general practice clinic is randomized using a computer algorithm and allocation is 1:1 between the AB or BA sequence. When an eligible clinic commits to the trial, the project statistician informs the project management about the next allocation in the allocation sequence and the clinic is randomized according to this, that is, blinded randomization allocation is used.

Randomization at the patient level is not considered feasible, as an ongoing randomization procedure in the clinic would be time consuming and pose a risk of bias and interference with the diagnostic procedure and subsequent decision-making by the GP.

Therefore, randomization is stratified by type of clinic, that is, partnership- or single-physician clinics. Large collaborative clinics are randomized as one unit in the group of non–single-physician clinics. A block randomization in blocks of 10 is used.

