### Statistical Analysis and Sample Size Calculations

#### Sample Size Calculation

Outcomes are on the individual patient level, and the clustering involves the entire GP clinic, not the individual GP. A balanced design with a common total cluster size and common period effect was adopted. As the study is a superiority trial, results from the feasibility study [16] and Danish national register data will inform the choice of parameters as inputs to the sample size formula derived by Li et al [19]. The intended effect size was fixed at a reduction from 0.32 to 0.28 based on the register results, which approximately corresponds to the distance between the median or mean to the 25th percentile. With a significance level of 0.05, power at 0.8, within-period within-cluster correlation of 0.02, and across-period within-cluster correlation as 0.01 to detect a difference between a prevalence of 0.32 recontacts in the control group and 0.28 in the intervention group, the sample size was calculated as 108 clinics, contributing 50 contacts each in the trial period. Pragmatically, the inclusion of 100 clinics was chosen.

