### Data Analysis

#### Effectiveness of GP Access to POC PCR

Demographic characteristics of the included patients and GP clinics will be presented. Analysis of the binary primary outcome uses a standard logistic regression model on the individual (contact) level, accounting for clustering of patients in clinics by generalized estimating equations. Primary analysis will follow an intention-to-treat approach, and we want to show superiority. A corresponding analysis strategy will be applied for hospital admissions, deaths, and redeemed antibiotic prescriptions. A level of 5% will be set as statistically significant. Analyses will be performed with the most recent version of Stata (StataCorp).

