## Abbreviations

ARI: acute respiratory infection
GP: general practitioner
ICER: incremental cost-effectiveness ratio
PCR: polymerase chain reaction
POC: point-of-care
RSV: respiratory syncytial virus
WP: work packages

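### The economic models name the GP as the cluster although clinics are randomised; if the bootstrap also resamples GPs, cost, effect and ICER intervals may be too narrow for multi-GP clinics

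*Protocol article*

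**What the plan says.** The Within-Trial Cost-Effectiveness section specifies separate generalized linear models for costs and effects: "The models will control for treatment, time point, treatment-by-period interaction as fixed effects, and cluster at the GP level as a random effect". The Abbreviations list reads "GP: general practitioner", so taken literally the random effect belongs to a physician. The same section takes the intervals for costs, effect and ICER as percentile limits from a 2-stage bootstrap with 1000 replications. It does not say what is resampled at the first stage.

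Three other places put the cluster at the clinic:

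- Allocation: "The study is designed as a cluster randomized crossover study with the GP clinic as the unit of randomization". All GPs of a clinic follow the same sequence, and "Large collaborative clinics are randomized as one unit in the group of non–single-physician clinics".
- Sample Size Calculation: "Outcomes are on the individual patient level, and the clustering involves the entire GP clinic, not the individual GP".
- Effectiveness of GP Access to POC PCR (primary analysis): "accounting for clustering of patients in clinics by generalized estimating equations".

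Clinics with several GPs are expected, because "randomization is stratified by type of clinic, that is, partnership- or single-physician clinics".

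**The concern.** GPs in a partnership clinic receive the device, lose it and cross over together. They are not independent replicates of the treatment contrast. A cluster set below the level of randomisation can count them as if they were, and the precision of the treatment difference is then overstated.

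The quantities at stake are the intervals for the cost, recontact and QALY differences, the ICER interval and the acceptability curve. The two work packages would also use different units for closely related outcomes: WP1 analyses 7-day recontact as a binary outcome clustered by clinic, while WP2 analyses the total number of recontacts over the same 7 days with the cluster set at GP level.

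**Working it through.** **Inputs**

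- From Sample Size Calculation: correlation 0.02 within period and 0.01 across periods, recontact proportions 0.32 and 0.28, alpha 0.05 (taken as two-sided), power 0.8, 108 clinics with 50 contacts each.
- Assumed, because the article does not say: *k* = 1 to 4 GPs per clinic, sharing the contacts equally and working in both periods; correlation between patients of different GPs in a clinic equal to that between patients of one GP; the recontact correlations applied to costs and QALYs.

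**Step 1: contacts per clinic-period.** The article gives no interval width or sample size for the economic analysis. Its only related figure is the 108 clinics, used here to judge whether the 50 contacts are per period or in total. With *m* contacts per clinic-period,

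clinics = (1.96 + 0.842)² × (0.32×0.68 + 0.28×0.72) × [1 + (m−1)×0.02 − m×0.01] / (m × 0.04²).

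- m = 25: 7.849 × 0.4192 × 1.23 / 0.04 = 101.2, or 104 with a continuity correction or t quantiles.
- m = 50: 7.849 × 0.4192 × 1.48 / 0.08 = 60.9, up to 64 across the variants.

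Neither gives exactly 108, but m = 25 is far closer and is used below. The gap to 108 does not bear on this point.

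**Step 2: GPs treated as independent clusters.** The variance factor for the within-clinic period difference is 1 + (m−1)×0.02 − m×0.01. If a clinic's GPs count as separate clusters, *m* is replaced by m/k.

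| GPs per clinic | Factor, clinic as unit | Factor, GP as unit | SE ratio |
|---|---|---|---|
| 1 | 1.230 | 1.230 | 1.00 |
| 2 | 1.230 | 1 + 11.5×0.02 − 0.125 = 1.105 | √(1.105/1.230) = 0.95 |
| 3 | 1.230 | 1 + 7.333×0.02 − 0.0833 = 1.063 | 0.93 |
| 4 | 1.230 | 1 + 5.25×0.02 − 0.0625 = 1.0425 | 0.92 |

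The SE is therefore about 5% to 8% too small for 2 to 4 GPs.

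**Step 3: simulated bootstrap.** Setting: 100 clinics, 24 contacts per clinic-period, 2000 runs, a continuous outcome with a small extra GP component (variance 0.01). Only the first stage of resampling was simulated.

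| GPs per clinic | Resample GPs: SE/true SE, coverage | Resample clinics: SE/true SE, coverage |
|---|---|---|
| 1 | 1.00, 95.2% | 1.00, 94.9% |
| 2 | 0.95, 93.4% | 0.99, 94.6% |
| 4 | 0.93, 93.3% | 1.00, 95.2% |

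The simulation error of each ratio is about 1/√(2×2000) = 1.6%, so this agrees with Step 2.

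**Step 4: the random effect on its own.** With 4 GPs per clinic, the model-based SE was 0.88 to 0.89 of the true SE with a GP intercept and 0.88 to 0.90 with a clinic intercept. Moving the intercept changes almost nothing. An intercept at either level cancels in the within-clinic period difference, and what is missing is the clinic-by-period component.

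**Step 5: dependence on that component.** If both correlations were 0.01, the factor would be 1 + (m−1)×0.01 − m×0.01 = 0.99 for any *m*, and the choice of unit would not matter. Simulated coverage with GP clusters was then about 96%. The protocol assumes 0.02 and 0.01, so by its own figures the component is present.

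**The case against.** The best defence is that GP here is shorthand for the practice. The article does mix the terms: Study Setting has GPs receiving reimbursement from the regions, whereas Recruitment and Eligibility Criteria has GP clinics receiving it. The section headed Effectiveness of GP Access to POC PCR clusters by clinic. The data sources described name no identifier for the treating physician, so a physician-level random effect may not even be feasible. This is plausible and cannot be ruled out. It does not clear the sentence, because the sample size section draws exactly this distinction for clustering: "the clustering involves the entire GP clinic, not the individual GP". An analyst who follows the economic section literally would use the level rejected there.

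A reader might go further and infer that the economic intervals **are** too narrow. The documents do not support that. The intervals come from the bootstrap and not from the random effect, and the first-stage unit is not stated. That omission alone is no fault, since an article commonly leaves such detail to the full analysis plan. The risk arises because the only cluster this section names is the GP.

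Three further readings also fail:

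- An understatement of 9% to 14% results from 50 contacts per clinic-period, which fits the 108 clinics poorly (Step 1).
- Nothing says that partnership clinics contribute the most patients per cluster; the sample size calculation assumes a common cluster size.
- Replacing GP by clinic in the random intercept would not by itself repair the SE (Step 4).

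**Conclusion.** The contradiction stands. The economic section states a cluster level that lies below the randomised unit, is rejected in the sample size section and differs from the primary analysis.

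The consequence is conditional and modest. If GPs are also the first-stage unit of the bootstrap, the SE for multi-GP clinics is about 5% to 8% too small, with coverage of a nominal 95% interval near 93%. If clinics are resampled, there is no narrowing from this source.

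The size rests on 2 to 4 GPs per clinic, 25 contacts per clinic-period, equal sharing of contacts among GPs in both periods, and recontact correlations carried over to costs and QALYs. None of these is documented for the economic outcomes. Because single-physician clinics are unaffected, the trial-wide effect lies between zero and these figures, depending on the unstated share of multi-GP clinics. The simulation covers the first resampling stage only; within-unit resampling at the second stage may add some variance. The primary analysis is not touched. The correction should be made, but it concerns a secondary analysis.

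**What to change.** 1. In Within-Trial Cost-Effectiveness, change the cluster term to: *cluster at the GP clinic level (the unit of randomisation), with a clinic-by-period effect*.
2. Add: *The first stage of the bootstrap resamples whole clinics, each with both of its periods.*

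The second change protects the reported intervals. The first removes the contradiction and lets the model carry the component that an intercept alone omits.

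The cost is two short edits and no new data. If GPs would otherwise have been resampled, intervals for multi-GP clinics widen by a factor of about 1/0.948 = 1.05 to 1/0.921 = 1.09; if clinics were always intended, the bootstrap intervals do not widen from the change of unit. The clinic-by-period variance may be estimated near zero for some outcomes, so the model should be checked for convergence.

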#### Questionnaire Data

The GPs or staff will distribute a leaflet with a QR code (and a link) to a web-based survey to all patients with ARI aged ≥15 years. For patients aged <15 years, the caregiver will be asked to answer the questionnaire. In the first questionnaire, the personal identification number and contact information will be collected, and the subsequent questionnaires will be distributed via a link in email and SMS text message at day 7, 14, and 28. In case of nonresponse, reminders will be sent within 2 days. Participants who complete all 4 questionnaires will be entered into a lottery for 1 gift card of Dkr 1000 for completing the first questionnaire and 1 gift card of Dkr 2500 for completing all 4 questionnaires. Questionnaires will be managed via a secure electronic questionnaire system (SurveyXact). Each questionnaire will take approximately 5 to 10 minutes to complete. Furthermore, a questionnaire will be sent to all participating GP clinics at the end of the trial followed by a reminder after 2 weeks in case of no response. The questionnaire will take approximately 5 minutes to complete. In it, the GPs will be asked about their overall experience of the equipment associated with (1) support for performing precise diagnostics, (2) support for clinical judgment, (3) the influence of the test results related to clinical management of patients, (4) the influence of the test results in patient communication concerning their condition, (5) disruption of consultation, (6) disruption in overall workflow, and (7) whether the equipment belongs in general practice. In addition, there is space for the GPs to write comments.

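### The percentile interval planned for the ICER has no rule for bootstrap replicates that cross a zero effect difference, where it stops being interpretable

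*Protocol article*

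**What the plan says.** All of this is in the protocol article, Within-Trial Cost-Effectiveness, unless noted.

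- The ICER is "expressed as the difference in costs divided by the difference in outcome, between patients in the intervention and control groups".
- There are two denominators: "Effect will be measured as the total number of recontacts within 7 days and quality-adjusted life years within 28 days".
- Uncertainty: "Nonparametric confidence intervals for costs, effect, and ICER will be computed using a 2-stage bootstrapping technique with 1000 replications", with the limits at "the 2.5th and the 97.5th percentile of the 1000 bootstrap replications".
- In addition: "Conventional methods for estimating uncertainty around the ICER, such as cost-effectiveness acceptability curves, will be applied as well".
- QALYs are "measured by EQ-5D-5L for patients aged >15 years". The restricted societal perspective, a sensitivity analysis, includes "productivity costs for patients or their caregiver (in case the patient is a child aged <15 y"). Questionnaire Data has the survey leaflet going "to all patients with ARI aged ≥15 years", with caregivers answering for younger patients.

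The section does not say what happens to the ICER interval when replicates have an effect difference near zero or of the opposite sign. It mentions neither net benefit nor Fieller limits.

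**The concern.** A percentile interval assumes that the replicates can be put in a meaningful order. Replicate cost differences and replicate effect differences can. Replicate ratios can only while the denominator keeps its sign. As the effect difference passes through zero the ratio runs to plus or minus infinity and returns from the other end. A negative ratio can then mean cheaper and better or dearer and worse, and a positive one dearer and better or cheaper and worse. Sorting such values and cutting off 2.5% at each end gives two numbers that do not bound a range of plausible cost-effectiveness.

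The question is whether that is likely in this trial. Two features suggest so: the effect on recontacts may be smaller than planned (the Introduction cites a meta-analysis in emergency departments that found no association with return visits), and a QALY difference accrued over 28 days is necessarily small. At stake is a cost per recontact avoided, or per QALY, published with limits that a reader would take at face value.

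**Working it through.** **1. Reproduce the sample size, to fix the contacts per period.** Inputs from Sample Size Calculation: 0.32 versus 0.28, alpha 0.05 (taken as two-sided), power 0.80, within-period correlation 0.02, across-period correlation 0.01, 50 contacts per clinic. With m contacts per clinic-period:

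clinics = (1.960 + 0.842)² × V × [1 + (m − 1)(0.02) − m(0.01)] / (m × 0.04²)

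Taking m = 25 (50 over both periods), the bracket is 1 + 0.48 − 0.25 = 1.23. With V = 2 × 0.32 × 0.68 = 0.4352 this gives 7.849 × 0.4352 × 1.23 / 0.04 = 105.04. With t quantiles on n − 2 degrees of freedom it gives 107.02, so 108, the stated figure. Taking m = 50 gives only about 61 to 64. So 25 per period is the reading that fits.

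**2. Standard error of the recontact difference**, at the 100 clinics chosen (2,500 contacts per condition):

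SE = √[(0.32 × 0.68 + 0.28 × 0.72) × 1.23 / 2500] = √(0.4192 × 1.23 / 2500) = 0.0144

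This uses the proportion with a recontact. The economic analysis counts total recontacts, for which the protocol gives no figures.

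**3. How often the denominator is close to zero.** For a true reduction d, the chance that its 95% interval includes zero is Φ(1.96 − d/SE) − Φ(−1.96 − d/SE). The share of wrong-sign replicates when the estimate equals d is Φ(−d/SE).

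| True reduction | d/SE | 95% interval includes zero | Wrong-sign replicates |
|---|---|---|---|
| 0.04 (planned) | 2.79 | 20% | 0.3% |
| 0.03 | 2.09 | 45% | 2% |
| 0.02 | 1.39 | 71% | 8% |
| 0.01 | 0.70 | 89% | 24% |

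If 50 contacts per period were meant, the SE would be √(0.4192 × 1.48 / 5000) = 0.0111, and the first and third rows of the interval column would be about 5% and 57%.

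**4. What the interval then looks like.** The protocol gives no cost figures. Assume a cost difference of EUR 10 with SE 3, independent of the effect, and normal replicates.

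- Reduction 0.04: the percentile limits are about EUR 87 to 855 per recontact avoided, around 10/0.04 = 250. This is usable.
- Reduction 0.02: about −3,650 to 4,700, around 10/0.02 = 500. About 92% of replicates are dearer and better, 8% dearer and worse, and almost none cheaper. The negative limit looks like possible savings but comes from the denominator changing sign.
- The mirror image (EUR −10, recontacts up by 0.02): about −3,600 to 4,700, nearly the same interval.

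**5. Net benefit on the same replicates.** At an illustrative EUR 100 per recontact avoided, net benefit is 100 × effect − cost, with SE √[3² + (100 × 0.0144)²] = 3.33. The dearer-and-better case gives 2 − 10 = −8, interval −14.5 to −1.5. The mirror case gives −2 + 10 = 8, interval 1.5 to 14.5. The two results separate cleanly.

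**6. QALY denominator.** Assume a mean utility gain of 0.01 over 28 days: 0.01 × 28/365 = 0.00077 QALY. With SE = SD × (28/365) × √(2/n), clustering and baseline adjustment ignored:

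| Utility SD (assumed) | Responders per arm (assumed) | SE | Wrong-sign replicates |
|---|---|---|---|
| 0.1 | 1,000 | 0.00034 | 1% |
| 0.1 | 250 | 0.00069 | 13% |
| 0.2 | 1,000 | 0.00069 | 13% |
| 0.2 | 250 | 0.00137 | 29% |

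**The case against.** The strongest reply is that the defect is conditional and the plan already surrounds it with sound measures. Much of this stands.

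- At the planned effect, with the estimate on target, only 0.3% of replicates have the wrong sign and the interval is usable. A reader might infer that the ICER interval is uninterpretable in every case; the figures do not support that.
- Coverage is not the problem. In simulations with the assumed costs (SE 3 or 8), the percentile interval covered the true ICER 96% to 98% of the time at reductions of 0.01 to 0.04, and 92% to 93% at 0.005, against 94% to 96% for Fieller limits. The fault lies in reading the interval.
- A reader might infer that the trial could report the same result for opposite conclusions. The plan does not allow that. It also gives intervals for costs and for effect separately; in the mirror example the cost intervals are 10 ± 1.96 × 3, about 4 to 16, against −16 to −4. The acceptability curves rest on net benefit and are unaffected.
- A reader might infer that the QALY ratio divides an all-age cost difference by an older-patient QALY difference. The protocol never says so. Adjustment for baseline utility could restrict the models to patients with EQ-5D data, caregiver productivity costs enter only the sensitivity perspective, and analysis-set detail may sit in a plan that is not shown.
- The age limit above 15 is best read as a symbol slip, since the same sentence explains that responsibility for one's own care starts at 15.

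What does not fall away is that the percentile rule for the ratio is stated outright, without a condition. The curves come in addition to that interval and do not replace it.

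**Conclusion.** The concern holds for the ICER interval alone. The stated rule is usable if nearly all replicates lie in one quadrant and uninterpretable if they span a zero effect difference, and nothing in the protocol distinguishes the two.

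The risk is realistic. For recontacts there is about a 20% chance that the denominator's 95% interval includes zero at the planned effect, and about 71% at half of it. This rests on 100 clinics, 25 contacts per period, the protocol's correlations, and the recontact proportion standing in for the count. For QALYs, about 1% to 29% of replicates have the wrong sign. That range rests on assumed inputs (gain 0.01, SD 0.1 to 0.2, 250 to 1,000 responders per arm); baseline-utility adjustment would normally lower it and clustering would raise it somewhat. The euro figures are illustrations only.

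This concerns a secondary objective and leaves the primary analysis, the cost and effect intervals and the acceptability curves intact. It is still worth correcting, because the change is nearly free and is better fixed before results are known. On the QALY population, only a clarification is warranted.

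**What to change.** Make the ICER interval conditional and add a measure that does not depend on a ratio:

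1. Report incremental net monetary benefit with bootstrap percentile intervals at stated willingness-to-pay values, for recontacts avoided and for QALYs.
2. Show it with the acceptability curves already planned and the replicates on the cost-effect plane.
3. Give a percentile interval for the ICER only when essentially all replicates fall in one quadrant. Otherwise give Fieller limits, which may themselves be unbounded when the effect difference is not clearly away from zero, or give no ICER interval.
4. State that costs and QALYs in the cost-per-QALY ratio come from the same patients, and align the age limit in Within-Trial Cost-Effectiveness with the one in Questionnaire Data.

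The cost is wording and a few lines of code. The same 1000 replicates serve throughout, and no new data are needed. The willingness-to-pay values have to be chosen in advance, including one for an avoided recontact.
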